### Bayesian inverse probability weighting

The intervention and control groups differ in characteristics and outcomes, and without randomisation, these differences can confound the results. The Directed Acyclic Graph (DAG) (figure 2) visually represents the relationships between the variables and helps to identify the confounders that need to be adjusted for in the analysis. A simplified generic DAG has been used initially; however, a specific DAG will be developed for each outcome. The DAG clarifies the causal pathways and ensures that we appropriately control for variables that could bias the results. To control for confounding effects, we use Bayesian inverse probability weighting, following these steps:

**Figure 2 F2:**
[figure not shown]
Simplified generic directed acyclic graph for hospital length of stay and parental stress.

A model will be created to predict treatment. Confounders identified with the DAG will be used as covariates to predict the probability of each patient being in the treatment group using a logistic regression (Bernoulli distribution), generating ‘propensity scores’. The regression model will be:

$$Treatment\;=\;\beta_{0}\;+\;\beta_{1}X^{T}+\varepsilon$$

where, $X^{T}$ is the matrix of confounders.

Samples of propensity scores will be generated: many propensity scores will be obtained from the posterior distribution.

Propensity scores will be converted into inverse probability of treatment weights using the formula:

$$\frac{\text{Treatment}}{\text{Propensity score}}+\frac{1-\text{Treatment}}{1-\text{Propensity score}}$$

An outcome model will be run using these weights: a Gaussian model will be used for numerical outcomes, and a cumulative probit model will be used for ordinal outcomes. The regression model used for the outcome analysis will be:

$$Outcome\;=\;\gamma_{0}\;+\;\gamma_{1}\times Treatment\;+\;\varepsilon$$

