## Methods and analysis

### Design

An observational prospective cohort study design was chosen, because it is not feasible to randomly assign patients to the intervention, as children are placed in a ward or the JPH based on the UMC where they are admitted. Random assignment to specific hospitals is not feasible given the practical impossibilities and negative impact of relocating children and families out of their own usual living environment.

The Strengthening the Reporting of Observational Studies in Epidemiology guideline will be used to report the study.^24^

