### Intervention group

The JPH is a separate building on the premises of the Amsterdam UMC. This TCU consists of eight separate family apartments and was opened in May 2022. Each apartment has its own bedroom for the child with medical complexity, a master bedroom for parents or caregivers, a living room, a bathroom, a kitchenette, a mezzanine level with a bed and desk for (if necessary) siblings and a private outdoor area. Furthermore, the JPH has different communal areas: a kitchen, living room with various workspaces, relaxation and play, a snuggle room, an adapted bathroom for persons with disabilities, a physiotherapy gym and a garden with playground. The JPH primarily serves children from the Amsterdam UMC, although children can be referred from hospitals in or outside the Amsterdam region.

In the JPH, at least one parent must be present 24/7, and siblings are also welcome to stay in the apartment. The TCU team consists of nurses, family counsellors and paediatricians. Additionally, we collaborate with other healthcare professionals, including allied health professionals, home care providers and pharmacy personnel in both the hospital and home settings. Nursing care and supervision of a dedicated paediatrician is available 24/7. In this form (24/7 parental stay and nursing care under the supervision of paediatricians), the JPH is unique in the Netherlands. During the stay, more and more responsibilities and tasks are gradually transferred to the parents until they become the primary caregivers. This process is guided by a newly developed structured care pathway, which is informed by the parental needs identified within our consortium.^3^ This care pathway outlines the transition process for parents and children as they move from being care recipients to taking on the role of care providers and coordinating their own care. It is organised into seven phases, each with a step-by-step transition plan (see online supplemental file 1 for more details). Personalised treatment goals are established based on the specific needs of both the child and the parents, facilitating a successful transition back home. These needs will vary for each family but can be categorised under overarching domains of care, namely physical, financial, psychological, social, spiritual and practical aspects such as medical devices, legal considerations and future/developmental aspects.

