### Control group

The control groups comprise patients and families who undergo the H2H transition directly from the hospital. This includes patients from the other four UMCs of the consortium. Patients from the Amsterdam UMC who transition directly from H2H without an intermediate stay in the JPH will also be included in the control group. Since there is no standardised care path, the H2H transitions vary across the different UMCs and even within different departments. There are no other TCUs in the Netherlands like the JPH; however, Erasmus MC offers one single-room apartment where parents can stay with their child for a weekend before being discharged home.^25^

A visual overview of differences between the intervention group and control group is presented in online supplemental file 1.

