### Additional analyses

Baseline patient characteristics and descriptive variables will be presented for the intervention and control group: age, gestational age, sex, diagnosis, underlying chronic condition, reason for admission, age patient during onset disease, medications after discharge, medical devices after discharge and amount of home care, medical day care or respite care. Parent characteristics include: age, gender, country of birth, ethnicity, Dutch speaking, marital state, educational and occupational level. Family characteristics include: number of children in the family, age of siblings, position of the index child within the family. To describe patient, parent and family characteristics, numerical data will be summarised using descriptive statistics: mean and SD for normally distributed data, median and quartiles for non-normally distributed data.

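### The weighted outcome model contains treatment only: valid if the propensity model is right, but it gives up precision and a second protection, and its interval carries no between-UMC uncertainty

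*Protocol article*

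**What the plan says.** The analysis is set out in the Protocol article under Bayesian inverse probability weighting.

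- **Propensity step.** "Confounders identified with the DAG will be used as covariates to predict the probability of each patient being in the treatment group". Uncertainty in the scores is carried forward, since "many propensity scores will be obtained from the posterior distribution".
- **Outcome step.** The weights go into an outcome model: "a Gaussian model will be used for numerical outcomes, and a cumulative probit model will be used for ordinal outcomes". The article then states "The regression model used for the outcome analysis will be" and prints Outcome = γ0 + γ1 × Treatment + ε. The equation has no covariate, no UMC term and no within-UMC correlation.

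Three other sections bear on the missing UMC term.

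- **Design:** "children are placed in a ward or the JPH based on the UMC where they are admitted".
- **Intervention group:** "The JPH primarily serves children from the Amsterdam UMC, although children can be referred from hospitals in or outside the Amsterdam region".
- **Control group:** "Since there is no standardised care path, the H2H transitions vary across the different UMCs and even within different departments". Amsterdam UMC also supplies some controls; their number is not given.

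The Sample size section plans about 150 patients, 50 in the intervention group and 100 in the control group.

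**The concern.** Two separate matters follow from the printed equation.

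**Covariates.** All confounding control rests on one model, the propensity model. If its form is wrong, or the weights leave imbalance by chance in a small sample, the error passes into γ1 with nothing to catch it. Adding the same confounders to the weighted outcome model gives a second chance of removing confounding. It also takes out outcome variation that would otherwise widen the interval. The article justifies its Bayesian approach by the limited data, so precision matters here.

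**UMC.** Treatment is nearly aliased with one hospital, and the article says that control care differs between hospitals. If outcomes correlate within a UMC, an interval from the printed model is too narrow, because it treats hospital differences as if they carried no uncertainty. The article chose credible intervals because they reflect uncertainty about the estimates.

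**Working it through.** **The plan's own figure.** The only number in the plan that bears on this point is n. Pilot accrual gives 44/6 × 18 = 132 patients at four UMCs, or 132 × 5/4 = 165 with a fifth. The stated 150 lies between them. It is a feasibility aim, is not disputed, and is used below as 50 + 100. The article gives no ICC, SD or confounder strength, so every size below rests on assumptions.

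**1. Covariates (simulation, 4,000 runs, n = 150, about one third treated)**

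Assumptions: four standard normal covariates. Two of them are confounders, with coefficient 0.5 each on the log-odds of treatment and on the outcome. Residual SD is 1, the true effect is 0 and there is no UMC correlation. Misspecification means that a quadratic term in one confounder is left out of the fitted model. The same weights were used with a treatment-only outcome model and with one that adds the covariates.

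| Scenario | Crude bias | Treatment only: bias (SD) | With covariates: bias (SD) |
|---|---|---|---|
| Both models right | 0.451 | 0.005 (0.211) | -0.004 (0.195) |
| Only propensity model wrong | 0.432 | -0.083 (0.247) | 0.001 (0.196) |
| Only outcome model wrong | 0.489 | 0.004 (0.247) | -0.011 (0.249) |
| Both wrong | 0.844 | 0.443 (0.315) | 0.463 (0.286) |

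Reduction in SD: 1 - 0.195/0.211 = 8% with both models right, and 1 - 0.196/0.247 = 21% with only the propensity model wrong. With only the outcome model wrong there is no gain in SD. With both wrong, both approaches stay biased.

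**2. UMC (closed form, before weighting)**

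Let ρ be the ICC. Take all 50 JPH children as belonging to the Amsterdam cluster and 20 controls in each of the five UMCs.

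Var/σ² = (1 - ρ)(1/50 + 1/100) + ρ × Σ(intervention share - control share)²

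The sum is (1 - 0.2)² + 4 × (0 - 0.2)² = 0.64 + 0.16 = 0.80. With independent errors, Var/σ² = 0.03.

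- ρ = 0.01: √[(0.0297 + 0.008)/0.03] = 1.12; a nominal 95% interval covers about 92%.
- ρ = 0.02: √[(0.0294 + 0.016)/0.03] = 1.23; about 89%.
- ρ = 0.05: √[(0.0285 + 0.040)/0.03] = 1.51; about 81%.

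The control mix matters. At ρ = 0.05, 40 Amsterdam controls and 15 at each other UMC give a sum of 0.36 + 4 × 0.0225 = 0.45, a ratio of 1.30 and 87% coverage. With no Amsterdam controls the sum is 1 + 4 × 0.0625 = 1.25, the ratio 1.74 and coverage 74%. At ρ = 0 the ratio is 1.

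If the JPH's own unit effect is counted as part of the intervention, only the control-site term ρ/5 remains. The ratios are then √[(0.0297 + 0.002)/0.03] = 1.03, √[(0.0294 + 0.004)/0.03] = 1.06 and √[(0.0285 + 0.010)/0.03] = 1.13. Coverage is about 94%, 94% and 92%.

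**The case against.** The strongest defence is that a treatment-only weighted regression is the standard marginal model, and it works when the propensity model is right: the simulation took a crude bias of 0.451 down to 0.005. This stands. A reader might infer that the plan ignores its measured confounders. It does not; they enter through the weights, and propensity uncertainty is propagated.

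A reader might also infer that leaving covariates out makes the interval too narrow. The check does not support that. Without UMC correlation, the treatment-only model covered 93% with normalised weights and 97% with a robust SE. Adding covariates alone lowered this to 88% and 93%. Any understatement from clustering comes from the missing UMC structure.

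On UMC, treating the JPH as a sixth independent cluster would give larger SE ratios of 1.18, 1.33 and 1.72. That does not fit clustering by admitting UMC, because most JPH children and some controls share Amsterdam. It is also fair to say that the question concerns this one named unit, so its own effect is arguably intervention rather than noise; the ratios then shrink to 1.03 to 1.13. A random intercept on five UMCs will depend on its prior. These points stand, and they place the UMC term in a sensitivity analysis rather than the main model.

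Two further limits apply. Independence of errors is read from the printed equation, not stated in words, and supplemental file 7, which holds the R code, is not shown. The usual double-robustness result is for weighted linear regression and does not automatically carry over to the cumulative probit model.

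Finally, the Additional analyses section lists post-discharge medications, devices and home care, and a reader might fear adjustment for variables that the JPH can change. That section says only "Baseline patient characteristics and descriptive variables will be presented for the intervention and control group"; it does not propose them as adjusters.

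**Conclusion.** The point holds as a worthwhile improvement to a valid analysis. The printed equation confines the confounders to the weights. Under the assumptions above, adding them to the outcome model lowers the SD by about 8% with a correct propensity model. It removes a bias of 0.083 residual SD and lowers the SD by about 21% when only that model is wrong. It does not rescue the analysis when both models are wrong.

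The interval also carries no between-UMC uncertainty. The direction is certain for any positive ICC, but the size is not known. It is about 1.12 to 1.51 times the SE for ICCs of 0.01 to 0.05 with the even control mix, and 1.03 to 1.13 if the JPH's unit effect is counted as intervention. The ICC, the confounder strength and the UMC mix are all assumed.

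**What to change.** **Main analysis.** Keep the weights and the posterior draws of the propensity score. Change the outcome model to Outcome = γ0 + γ1 × Treatment + γ2 × (pre-treatment DAG confounders) + ε, using the confounder set already named for each outcome's propensity model. Report the treatment contrast standardised over the study population, so that the marginal estimand is kept; this matters most for the cumulative probit model. State how the credible interval is obtained, since covariate adjustment did not by itself give nominal coverage in the simulation.

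**Sensitivity analyses.** (a) Add a random intercept for UMC of admission, with a stated prior on its SD that is varied over a range. (b) Compare JPH children with Amsterdam controls only, reporting how many there are. State that five UMCs, with treatment nearly aliased with Amsterdam, cannot fully separate the JPH effect from the Amsterdam effect.

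**Cost.** Analysis text and some extra programming; no new data beyond the confounders that the propensity model already needs. Intervals in the first sensitivity analysis may be wider, and the Amsterdam-only comparison will be imprecise if few controls come from there.

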### Additional analyses

Baseline patient characteristics and descriptive variables will be presented for the intervention and control group: age, gestational age, sex, diagnosis, underlying chronic condition, reason for admission, age patient during onset disease, medications after discharge, medical devices after discharge and amount of home care, medical day care or respite care. Parent characteristics include: age, gender, country of birth, ethnicity, Dutch speaking, marital state, educational and occupational level. Family characteristics include: number of children in the family, age of siblings, position of the index child within the family. To describe patient, parent and family characteristics, numerical data will be summarised using descriptive statistics: mean and SD for normally distributed data, median and quartiles for non-normally distributed data.

### Sample size

To assess the largest possible sample size within the available resources, the original plan involved enrolling all eligible patients over a span of 1.5 years, with the aim of accruing approximately 150 patients (50 in the intervention group and 100 in the control group).

The numbers are based on our previous pilot study: H2H transition of CMC in the Netherlands: current practice.^52^ In this study, the same population was included and the objectives were to (1) describe the demographics, clinical characteristics and course of patients who are in the H2H transition and (2) identify perceived barriers for postponement of H2H transition (METC Amsterdam UMC reference number W21_581 # 22.025). This study enrolled 44 patients over a period of 6 months at four UMCs (Amsterdam UMC, EMC, UMCG, Radboud UMC). In the BRIDGE study, parents are asked to fill in questionnaires, which may result in fewer parents willing to participate. However, to compensate for this, an additional UMCU has been included.

### Study limitations

This study protocol faces several inherent limitations. First, the substantial time commitment for parents, approximately 50 min at discharge home, may discourage those with high stress levels from participating. This could result in an under-representation of highly stressed parents, particularly in the control groups, given the hypothesis that parents in the JPH group experience less stress. Second, the exclusion of families with limited proficiency in both English and Dutch may result in a skewed representation of the population. These excluded families, often facing distinct challenges in the transition from H2H, represent a potential gap in our understanding of their H2H experience. Third, the decision to exclude patients who are transferred to another out-of-hospital facility might have the consequence that the different groups are less comparable because the included control group might be less care-intensive (because they can be discharged home directly instead of having to stay in an out-of-hospital facility for a period). Finally, a limitation is that despite the use of Bayesian inverse probability weighting, there may still be unmeasured confounding variables that could affect the results. The impossibility of randomly selecting the intervention, of course, is the biggest issue to this matter. A careful selection of control patients may help decrease the chances of bias.

### Trial status

Currently, all five UMCs are enrolling patients. Recruitment began in December 2023 at the JPH and Amsterdam UMC, followed by UMCG in January 2024, Radboud in March 2024, EMC in April 2024 and UMCU in September 2024. Final inclusion of the BRIDGE study is expected in 2026.
